## Abstract

Early initiation of palliative care in patients with advanced chronic conditions significantly improves their quality of care; however, variability in disease trajectories complicates such interventions’ timing. The NECPAL CCOMS-ICO prognostic tool was developed as a straightforward instrument to help healthcare providers in all clinical settings promptly identify patients with advanced chronic conditions who require palliative care, thereby enhancing service planning and delivery. Its latest version, 4.0, 2021, for the first time, incorporates a patient survival estimation. Nevertheless, validation is necessary. This study aims to validate the NECPAL version 4.0 tool in an independent cohort. It is an observational, prospective study involving outpatients and hospitalized non-randomized patients at Hospital Universitario Infanta Leonor–Virgen de la Torre in Madrid, Spain, all of whom have at least one advanced chronic condition. The study is scheduled to last 6 years, including a recruitment period of 30 months starting 1 February 2024, followed by a 12-month follow-up period for each patient. This is the first prospective study designed to validate the NECPAL version 4.0 instrument. Implementing this tool would allow the identification of patients with advanced chronic conditions and unmet palliative care needs and determine the more appropriate care pathway at the proper moment.

## 1. Introduction

In economically developed countries, most people now die from complex long-term illnesses such as cancer, respiratory and heart diseases, stroke, and dementia [1]. These conditions are characterized by gradual progression, prolonged duration, and prognostic uncertainty. Identification of patients with a life-limiting illness when they are starting to need a change in their goals of care contributes to end-of-life care planning.

The World Health Organization (WHO) underlines the importance of providing palliative care (PC) early in the disease trajectory of patients suffering from a life-limiting illness [2]. Evidence shows earlier access to PC promotes quality of life, reduces hospitalizations, and even prolongs survival [3,4,5,6,7,8,9,10,11]. However, the WHO estimates that only 14% of patients with life-limiting diseases who need PC receive it [4]. In this setting, patients should not only be treated at the final stages of their disease but before. The concepts of “first transition”, “second transition”, and “third transition” have been developed to address the evolving needs of patients with advanced chronic illnesses (Figure 1). The “first transition” emphasizes integrating PC at the onset of a chronic or life-limiting diagnosis, aiming to manage symptoms and enhance life quality from the beginning. The “second transition” arises as the patient’s condition becomes more complex, necessitating specialized PC services for advanced symptom control and intensive psychosocial support. The “third transition” represents the final stage, centering on end-of-life care focusing on comfort, dignity, and emotional and spiritual support, ensuring a peaceful closure for patients and their families [12].

A systematic method could facilitate the early identification of patients with advanced progressive illnesses likely to have unmet PC needs and facilitate end-of-life care planning.

The Surprise Question (SQ) has been proposed as a prompt for the early identification of patients who may benefit from PC. It involves a single reflective query: “Would you be surprised if this patient were to die within the next 6 to 12 months?” Given its simplicity and lack of reliance on complex scoring systems, the SQ has been widely adopted in clinical practice to help healthcare professionals identify patients with potential PC needs. Nevertheless, its subjective nature means that its accuracy may vary depending on both the characteristics of the patient population and the clinician’s judgment. In contrast, the Palliative Care Screening Tool (PCST) offers a more structured approach. It integrates clinical variables—such as functional status and comorbidities—into a scoring algorithm that estimates the patient’s expected survival time. While both the SQ and PCST are established instruments used to support clinical decision-making in the context of PC, comparative data regarding their prognostic performance remain limited. Emerging evidence suggests that using these tools in combination may yield greater predictive accuracy than employing either tool independently.

Identifying patients likely to have unmet PC needs should focus on anticipating their needs and predicting functional decline to create a plan proactively. In this setting, several screening tools have been developed (Table 1). Most tools use either prediction of death or deterioration or both to identify patients. Some tools are applicable in both primary care and hospital settings. Moreover, some utilize the SQ alongside other indicators for a thorough evaluation, while others are tailored to specific patient conditions and do not have a fixed cutoff value. Nevertheless, evaluating these tools is limited because of a lack of a valid comparator, so their actual clinical utility is still being determined [13,14,15]. Further research on effective strategies for identifying patients with potential PC needs would be beneficial.

As the early identification of patients in need of PC could meet patients’ treatment goals and improve their quality of life, it is imperative to screen these patients using a highly accurate screening tool. The NECPAL CCOMS-ICO tool, developed by the Catalan Institute of Oncology in Spain, aims to identify early patients with advanced chronic conditions requiring PC across the healthcare system [16]. This instrument can be used in outpatient and in-hospital environments. It combines a simple SQ, ‘Would you be surprised if this patient died within the next 12 months?’, with six parameters. The parameters of the NECPAL instrument include (1) Palliative Needs Identified, where healthcare professionals determine if the patient requires PC; (2) Functional Decline, assessing the patient’s ability to perform daily activities; (3) Nutritional Decline; (4) Multi-Morbidity, indicating the presence of more than two chronic diseases added to the principal condition; (5) Use of Resources, relating to the frequency of emergency admissions or increased demand for medical interventions within six months; and (6) Specific Disease Criteria, which assesses the severity or progression of the specific chronic conditions. A patient is NECPAL+ if the SQ is answered positively (SQ+) and at least one parameter is met. Its latest version, 4.0, 2021, for the first time, incorporates a patient survival estimation (Supplementary Materials). NECPAL+ patients are categorized into three prognostic stages to estimate survival: Stage I (SQ+ and 1–2 parameters), with an estimated survival of 38 months; Stage II (SQ+ and 3–4 parameters), with 17.2 months; and Stage III (SQ+ and 5–6 parameters), with 3.6 months (Supplementary Material S1) [17]. Incorporating mortality and prognosis assessments into the tool could more accurately pinpoint the optimal time to initiate PC. However, external validation is essential to improve their clinical performance.

## 2. Aims and Objectives

This prospective observational cohort study aims to investigate the accuracy of the NECPAL version 4.0 (2021) tool—developed by the NECesidades PALiativas, a Collaborating Centre of the World Health Organization at the Catalan Institute of Oncology—in identifying patients with advanced chronic conditions who require early PC and analyzes its effectiveness as a mortality predictor.

### 2.1. Primary Objectives

Two primary objectives of the research are considered:a.To explore, in an accessible population of patients assisted within the Community of Madrid, Spain public health system, the proportion of patients with advanced chronic illnesses who require PC using the NECPAL version 4.0 (2021) tool.b.To investigate the instrument’s accuracy in predicting mortality in this population.

### 2.2. Secondary Objectives

a.To describe in this population the functional and nutritional deterioration, the prevalent advanced chronic diseases, the demand and need for PC by the patient, their family, and the professional.b.To compare the perceived quality of life among NECPAL+ patients receiving PC, those not receiving it, and NECPAL- patients using the EuroQol 5D tool (EQ-5D).

### 3.2. Setting

The study is planned to span six years, including a recruitment period of 30 months followed by a 12-month follow-up period for each patient. Patients will be recruited from both outpatient consultations and hospital admissions.

### 3.3. Participants

Patients with advanced chronic conditions will be invited to take part in the study. Oral and written information will be given.

#### 3.3.1. Inclusion Criteria

Patients are eligible for inclusion in the study if they fulfill the following criteria: adult (at least 18 years of age) with cancer or non-oncological advanced chronic condition. Non-cancer advanced chronic conditions are defined as progressive and incurable diseases with no reasonable possible therapeutic response by the criteria established by the Spanish Society of Palliative Care (SECPAL) [19]. These conditions include target organ damage, such as heart, pulmonary, liver, and kidney diseases; neurodegenerative disorders, dementia, and cerebrovascular disease; and peripheral vascular illnesses (Table 2). Cancer describes neoplasms that cannot be cured [20,21].

#### 3.3.2. Exclusion Criteria

a.Patients who are likely to be transferred to other facilities or expected to move out of the hospital’s geographic area during the study period.b.Patients with a projected life expectancy of less than 3 months. Patients with an estimated life expectancy of less than three months are excluded from this study, as the NECPAL version 4.0 tool is designed for the early identification of patients with advanced chronic conditions who may benefit from anticipatory palliative care planning. The prognostic stratification provided by the tool begins at a minimum horizon of three months (Stage III), and including patients with a shorter expected survival could impair the assessment of its predictive performance and clinical applicability in earlier stages of disease. This criterion ensures that the study remains focused on the population for whom proactive palliative interventions may still have a meaningful impact.

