### 3.5. Principal Outcome Measures

Predictive accuracy of NECPAL version 4.0 (2021) tool for identifying patients who need PC.Mortality prediction accuracy at 3, 17, and 38 months.Quality of life.

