### 3.7. Data Variables

#### 3.7.1. Primary Dependents Variables

Positive NECPAL identification.Mortality at 3, 17, and 38 months.

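### Excluding patients projected to live under 3 months selects on a prediction of the 3-month mortality outcome, and the stated reason treats Stage III's estimated survival as a floor

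*Protocol article*

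**What the plan says.** Section 3.3.2 of the protocol article excludes "Patients with a projected life expectancy of less than 3 months". It gives several reasons: the tool is meant for early identification, patients near death could impair the assessment in earlier stages, and the study should stay with people for whom proactive care may still matter. It adds that "The prognostic stratification provided by the tool begins at a minimum horizon of three months (Stage III").

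The Introduction gives the survival estimates that version 4.0 attaches to the three stages. For the group with the worst prognosis it reads "Stage III (SQ+ and 5–6 parameters), with 3.6 months". The other two estimates are 38 months for Stage I and 17.2 months for Stage II. It does not say whether these are medians or means.

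Primary objective (b) in section 2.1 is "To investigate the instrument’s accuracy in predicting mortality in this population". Section 3.5 lists "Mortality prediction accuracy at 3, 17, and 38 months" among the principal outcomes, and section 3.7.1 names "Mortality at 3, 17, and 38 months" as a primary dependent variable. Section 5.2 assesses NECPAL+/− against mortality at each of these times by sensitivity, specificity, PPV and NPV. None of these sections limits the 3-month result to patients who were expected to live at least 3 months.

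**The concern.** There are two linked problems.

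First, the three-month minimum does not agree with the Introduction. An estimated survival of 3.6 months is a central figure for Stage III. A sizeable share of a group with that survival would die before 3 months, so those early deaths belong to the prognosis the tool gives for Stage III.

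Second, the criterion filters entry by a forecast of the event that defines the 3-month outcome. The forecast also overlaps with the tool. A clinician who projects death within 3 months would hardly be surprised by death within 12, so these patients are very likely SQ+ (section 4), and one positive parameter then makes them NECPAL+. Excluding them takes out mainly true positives for 3-month death.

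At stake is how the results are read. A well-calibrated tool could appear to overstate early mortality in Stage III and to miss a larger share of 3-month deaths. The NECPAL+ proportion in objective (a) would also describe a population from which likely positives had been removed.

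**Working it through.** **The plan's own figure.** The article gives no expected 3-month mortality to reproduce. Its sample size does reproduce: 1.96² × 0.5 × 0.5 / 0.05² = 384.2, and 384 × 1.10 = 422.4, against about 420. It rests on a single proportion and says nothing about 3-month deaths.

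**Inputs.** From the Introduction: estimated survival of 38, 17.2 and 3.6 months for Stages I, II and III. From section 3.3.2: the 3-month threshold. Curve shape and accuracy of projection are assumptions, because the article gives neither.

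**Step 1: deaths by 3 months with no exclusion.** Reading the estimates as medians, P(T < 3) = 1 − 2^(−(3/median)^k), where k = 1 is exponential.
- Stage III, k = 1: 1 − 2^(−3/3.6) = 0.439. With k = 1.3 it is 0.421; with k = 0.7 it is 0.457.
- Stage III, if 3.6 is an exponential mean: 1 − e^(−3/3.6) = 0.565, or about 57%.
- For comparison, k = 1: Stage II, 1 − 2^(−3/17.2) = 0.114; Stage I, 1 − 2^(−3/38) = 0.053.

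So Stage III carries by far the highest 3-month risk, and three months is not a floor for it.

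**Step 2: Stage III after the exclusion.** Let f be the share of Stage III patients dying before 3 months who are excluded, with no survivors wrongly excluded (exponential, median 3.6). The share retained is R = 1 − 0.439f. Three-month mortality is 0.439(1 − f)/R. The median solves 2^(−t/3.6) = R/2, so t = 3.6 × log2(2/R).

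| f | R | 3-month mortality | Median (months) |
|---|---|---|---|
| 0 | 1.000 | 44% | 3.6 |
| 0.25 | 0.890 | 0.329/0.890 = 37% | 4.2 |
| 0.50 | 0.781 | 0.219/0.781 = 28% | 4.9 |
| 0.75 | 0.671 | 0.110/0.671 = 16% | 5.7 |

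**Step 3: wrongly excluded survivors.** If f = 0.50 and 20% of 3-month survivors are also excluded, 3-month mortality is 0.219/(0.219 + 0.8 × 0.561) = 33%. The median solves 0.8 × 2^(−t/3.6) = 0.668/2, giving 4.5 months. The shift is smaller but in the same direction.

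**Step 4: direction for NECPAL+ sensitivity at 3 months.** Suppose a share g of all 3-month deaths is excluded and all of these would have been NECPAL+. Sensitivity moves from Se to (Se − g)/(1 − g). With an assumed Se of 80%, it becomes 0.55/0.75 = 73% for g = 0.25 and 0.30/0.50 = 60% for g = 0.50. If Se were 100% it would not change. This is an illustration; the article gives no value for Se or g.

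**The case against.** The exclusion is openly reasoned, and three of its reasons do not depend on the three-month minimum. Every estimate is conditional on its eligibility criteria, which are published. The disputed sentence might also mean only that 3 months is the shortest of the three assessment times. These points stand in part: restricting the study to earlier identification is a legitimate choice, and the wording may be loose rather than a claim that nobody in Stage III dies sooner. But the sentence ties the minimum to Stage III's prognosis and uses it to justify removing early deaths, while the 3-month outcome is kept without any condition. The earlier-stage argument is also weak, because stages are set by parameter count and Stages I and II can be reported separately without excluding anyone.

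A reader might infer more than the article supports:
- **That the criterion removes much of Stage III.** This depends on how accurately survival is projected, which is not given.
- **That Stage III survival is a stated primary target.** It is one only by implication, through the aim of validating version 4.0. Section 5.2 applies the accuracy measures to NECPAL+/−, not to stages.
- **That observed Stage III survival must exceed 3.6 months even if the tool is right.** The article does not show whether the cohort behind that figure had a similar exclusion. If it did, the shift against 3.6 months would shrink or disappear.
- **That 3-month sensitivity would rest on deaths nobody foresaw.** The Surprise Question looks 12 months ahead. A patient projected to live 6 months who dies at 2 would still be SQ+.

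**Conclusion.** The point holds as a matter of rationale and interpretation. The three-month minimum does not match the Introduction's 3.6-month estimate, and the criterion selects on a prediction of a principal outcome that is not stated as conditional. The direction (lower 3-month mortality, PPV, sensitivity and NECPAL+ proportion; longer observed Stage III survival) needs only that projections are better than chance and that excluded patients are mostly NECPAL+.

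The size is not known. The fall in Stage III 3-month mortality from 44% to between 37% and 16%, with medians of 4.2 to 5.7 months, assumes an exponential curve, 3.6 months as a median, 25% to 75% of early deaths excluded and no survivors wrongly excluded. It describes a shift relative to the same cohort without the exclusion. It is a shift relative to the published 3.6 months only if the source cohort had no comparable criterion. Nor does the article support concluding that the criterion must be dropped: changing the population partway through recruitment has its own costs.

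**What to change.** 1. Correct the sentence in section 3.3.2 so that it no longer presents three months as the lower limit of Stage III, and reconcile it with the Introduction.
2. In sections 2.1, 3.5 and 5.2, state 3-month accuracy, any Stage III survival comparison and the NECPAL+ proportion as conditional on a clinician-projected life expectancy of at least 3 months. Do not present them as an unconditional validation of the 3.6-month figure.
3. Report how many patients were excluded under this criterion, taken from the eligibility checklist that section 3.4 already requires for all considered cases. Add their NECPAL stage only where it is already in routine records, because section 6.1 rules out study procedures before consent is signed.

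The cost is rewording, a count from an existing form and a narrower claim. Whether to keep the criterion is for the sponsor to reconcile with the 3-month outcome. Separately, section 4 attaches the 3-month assessment to Stage I and the 38-month one to Stage III, the reverse of the Introduction; these passages must also be reconciled.

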### 3.4. Patients Recruitment

Investigators will identify potential participants through electronic health records in various settings, including outpatient consultations, hospitalized patients, or follow-up visits. Principal Investigators will complete an eligibility criteria checklist for all considered cases. Clinical information will be used to assess eligibility. To ensure a fair and objective study, patients will be stratified based on age, gender, underlying chronic conditions, and NECPAL tool results (positive or negative) to create balanced groups.

At the time of writing this manuscript, 105 patients were included in the study.

### 3.5. Principal Outcome Measures

Predictive accuracy of NECPAL version 4.0 (2021) tool for identifying patients who need PC.Mortality prediction accuracy at 3, 17, and 38 months.Quality of life.

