## 4. Study Procedures

The study is being conducted at Hospital Universitario Infanta Leonor-Virgen de la Torre, a secondary-level hospital in Madrid, Spain, involving outpatients and inpatients. Eligible participants are adults aged 18 years or older with at least one advanced chronic condition or cancer, identified by physicians through electronic medical records. Advanced chronic conditions are defined, according to the criteria established by SECPAL guidelines (Table 2). Cancer describes neoplasms that cannot be cured. Physicians apply the NECPAL tool to each case, beginning with the SQ, which asks, “Would you be surprised if this patient were to die in the next 12 months?”. If the healthcare professional answers “no” to this question, the patient is considered SQ+. To be considered NECPAL+, an SQ+ patient must also meet at least one parameter from the NECPAL tool. If the professional answers “yes” to the SQ (SQ−), or if an SQ+ patient does not meet any additional NECPAL parameters, the patient is classified as NECPAL−. All patients classified as NECPAL+ are deemed to need PC. It is recorded whether the NECPAL+ patient is receiving PC or not. Mortality status (alive or deceased) is assessed and recorded at 3 (NECPAL stage I), 17 (NECPAL stage II), and 38 months (NECPAL stage III), including the date and cause of death, if applicable. Mortality data are collected through telephone follow-ups and chart reviews. The quality of life of the study population is assessed using the EuroQol-5D-5L instrument (EuroQol Research Foundation, Rotterdam, The Netherlands). The questionnaire is administered at inclusion, 3 (NECPAL stage I), 17 (NECPAL stage II), and 38 months (NECPAL stage III), if applicable. Quality of life is compared among NECPAL+ patients receiving PC, those not receiving it, and NECPAL− patients. No assessments beyond those required for usual care are conducted.

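### Accuracy of NECPAL 4.0 for palliative care need is a principal outcome, but the protocol names no reference standard for need that is independent of the tool

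*Protocol article*

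**What the plan says.** Section 2 gives the study two targets: the accuracy of the tool "in identifying patients with advanced chronic conditions who require early PC and analyzes its effectiveness as a mortality predictor". Section 3.5 keeps them apart, listing "Predictive accuracy of NECPAL version 4.0 (2021) tool for identifying patients who need PC" first and mortality prediction second. Section 3.1 does the same.

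The text that puts the first target into practice reads differently:

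- Section 4 sets need by the test result: "All patients classified as NECPAL+ are deemed to need PC".
- The Introduction defines a positive result: "A patient is NECPAL+ if the SQ is answered positively (SQ+) and at least one parameter is met". The first of the six parameters is "Palliative Needs Identified, where healthcare professionals determine if the patient requires PC".
- Primary objective (a) in Section 2.1 asks for "the proportion of patients with advanced chronic illnesses who require PC using the NECPAL version 4.0 (2021) tool", which is a proportion and not an accuracy.
- The matching dependent variable in Section 3.7.1 is "Positive NECPAL identification", the test result itself.
- Section 5.2 plans sensitivity, specificity, PPV and NPV, all against death at 3, 17 and 38 months.

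**The concern.** To estimate how accurately a tool identifies a condition, one must know who has the condition from something other than the tool. Here the tool's positive result serves both as the test and as the definition of need.

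At stake is what the study may conclude. A report that follows Section 3.5 as worded would have to put either the NECPAL+ proportion or the accuracy for mortality under the heading of accuracy for palliative care need. Neither shows that the tool finds the patients who need palliative care. The Discussion itself says that identification should not rest on mortality prediction alone, yet death is the only reference against which accuracy is planned.

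**Working it through.** **1. Could anything recorded serve as an independent reference for need?**

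| Candidate | Where | Why it does not serve as written |
|---|---|---|
| Deemed need | Section 4 | It is the test result |
| Professional's judgement of need | Introduction | It is parameter 1 of the test |
| Demand and need of patient, family and professional | Section 2.2(a) | To be described only; not named as a reference, and no accuracy analysis is attached |
| Receipt of palliative care | Section 4 | Receipt is not need; Section 4 specifies recording it for NECPAL+ patients |
| Later re-evaluation of NECPAL− patients | Section 4 | Not captured prospectively in the study database |
| Death at 3, 17 and 38 months | Section 5.2 | The reference for the second target, mortality |

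**2. The two-by-two table.** Let P be the number of NECPAL+ patients, M the number of NECPAL− patients, and u the share of NECPAL− patients who have need. Every NECPAL+ patient is deemed to have need, so true positives = P and false positives = 0. False negatives = uM and true negatives = (1 − u)M. Then:

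- PPV = P / (P + 0) = 100%
- specificity = (1 − u)M / [(1 − u)M + 0] = 100% for any u below 1
- sensitivity = P / (P + uM)
- NPV = 1 − u

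PPV and specificity are fixed by definition. Sensitivity and NPV depend on u, which the study does not observe.

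**3. Size.** The total of 420 is the target in Section 5.1. The documents give neither the NECPAL+ share nor u, so both are assumed here.

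| NECPAL+ share (assumed) | P | M | Sensitivity, u = 0 | u = 10% | u = 30% | u = 50% |
|---|---|---|---|---|---|---|
| 20% | 84 | 336 | 100% | 71% | 45% | 33% |
| 50% | 210 | 210 | 100% | 91% | 77% | 67% |
| 80% | 336 | 84 | 100% | 98% | 93% | 89% |

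For example, with a 20% share and u = 50%: 84 / (84 + 0.5 × 336) = 84 / 252 = 33%. NPV falls from 100% to 50% over the same range of u. The study data cannot say which column applies.

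**4. What the sample size supports.** Section 5.1 uses Z = 1.96, E = 0.05 and p = 0.5: n = 1.96² × 0.5 × 0.5 / 0.05² = 384.2. With the finite-population correction for 350,000, n = 384.2 / (1 + 383.2 / 350,000) = 383.7. Both agree with the stated 384. Adding 10% gives 384 × 1.10 = 422, and dividing by 0.90 gives 427; the stated figure is approximately 420. The calculation reproduces. It gives the precision of one proportion, which fits objective (a), and involves no accuracy measure.

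**The case against.** The strongest reply is that the working parts of the plan already agree with one another. Objective (a) is a proportion obtained with the tool, the dependent variable is the tool result, the sample size is for one proportion, and accuracy measures are confined to mortality. The Introduction also says openly that tools of this kind lack a valid comparator. On this view the fault is loose wording in a few places and no planned analysis fails. This largely stands: the problem is a mislabelled outcome. It does not remove the point, because the aim and the first principal outcome govern what will be claimed.

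Three stronger readings are tempting, and the protocol does not support them:

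- *All four accuracy measures are 100% by construction.* Section 4 says that NECPAL+ patients are deemed to need palliative care. It does not say that NECPAL− patients do not, and it allows that their needs may change. Only PPV and specificity are fixed without a further assumption.
- *The tool result is the only mention of need.* Section 2.2(a) also covers need as seen by patient, family and professional. It is to be described and is not used as a reference standard.
- *The outcome carries no information.* The NECPAL+ proportion attached to it is informative; its label is wrong.

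It could also be said that a statistical analysis plan or the full protocol may name the reference. The point, however, is not an omitted detail. The article itself states how need is determined, and Section 4 says that no assessments beyond usual care are made. A later document would have to override that definition.

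**Conclusion.** The point holds in this form: accuracy for identifying patients who need palliative care cannot be estimated under the protocol as written. PPV and specificity for need are 100% by definition. Sensitivity and NPV are either 100%, if NECPAL− is taken to mean no need, or not identifiable. The sensitivity range of 33% to 100% rests on an assumed NECPAL+ share of 20% and an assumed 0 to 50% of NECPAL− patients in need; the conclusion does not depend on those values. The proportion NECPAL+ and the accuracy measures against mortality are separate quantities, and this argument does not affect them. What changes is the conclusion that the study may draw about need.

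**What to change.** - In Section 3.5, replace the first outcome with the proportion of eligible patients classified NECPAL+, overall and by stage. This matches objective (a), the dependent variable in Section 3.7.1 and the sample size in Section 5.1.
- In Section 2 and objective (a), describe these patients as NECPAL+ and not as requiring palliative care, and bring Section 3.1 into line.
- Use the word accuracy for mortality only, and state that validity for palliative care need is not tested.
- Reconcile Section 3.4, which stratifies patients on the NECPAL result, among other factors, to obtain balanced groups. If that steers recruitment, the NECPAL+ proportion is partly set by design and the replacement outcome is not a clean estimate either. State that the stratification applies to the analysis only.

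The cost is a narrower claim and a documented amendment, since 105 patients were already included when the article was written. No new data or assessors are needed.

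If the sponsor wishes to keep the accuracy claim, the alternative is a reference standard for need that is independent of the tool and assessed blind to its result in both NECPAL+ and NECPAL− patients, with its own analysis and precision calculation. That costs far more. If it called for assessments outside usual care, it would also conflict with the statement in Section 4 that none are made.
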